#### MINI International Neuropsychiatric Interview (MINI)

The MINI is a diagnostic structured interview for the assessment of psychiatric diagnoses [70], with a corresponding German version [75]. The specificity of the MINI was reported as good for all diagnoses (ranging from 0.72 to 0.97) [70]. In this study, a part of the MINI (depressive episode, suicidality, manic episode, and psychosis) was also administered via telephone.

#### Paranoia Checklist

The Paranoia Checklist was developed by Freeman et al. in 2005 [76] and assesses the frequency, degree of conviction, and associated distress of a wide range of paranoid thoughts. The three subscales each include the same 18 items, which are rated on a five-point Likert scale: The first subscale measures the frequency of paranoid thoughts (ranging from ‘does not apply at all’ to ‘applies very well’; adapted), the second subscale measures the degree of conviction (from ‘not at all convinced’ to ‘absolutely convinced’) and the third subscale surveys the level of distress (from ‘not distressing’ to ‘very distressing’). Cronbach’s alpha, as an estimate of reliability, is reported as .90 or above, which stands for an excellent internal consistency of the Paranoia Checklist [76].

#### Launay–Slade Hallucination Scale (LSHS-R)

The LSHS-R is the revised version of the LSHS, developed by Launay and Slade in 1981 [77]. It includes 12 items and measures the predisposition to hallucinations on a wide spectrum [78]. There is a German version of the LSHS-R, which shows a Cronbach’s alpha of .87 in a patient sample and therefore is comparable to the original [79]. The five-point Likert scale ranges from 0 (‘certainly does not apply to me’) to 4 (‘certainly applies to me’) and there is a sum score that will be compared between both groups of participants.

### Secondary outcome measures

#### Delusion and Voices Self-Assessment (DV-SA)

The DV-SA has two subscales, a Delusions Scale (DS) and a Voices Scale (VS). The former contains five items to assess patients' opinions about the dominant delusional idea and the latter includes ten items about the subjective dimensions of auditory hallucinations [80]. All responses of the participants are rated on two four-point Likert scales, from 0 (absence of problems) to 3 (the severest of problems), with the highest achievable total score of 15 for the DS and 33 for the VS [80]. For this study, we changed the time period referenced in the DV-SA from 1 month to 1 week.

#### Incongruence questionnaire (K-INK)

The K-INK [81] is a short version of a questionnaire (INK) that measures the degree of realization of motivational goals in the participant’s life. Those goals can be classified into two groups: approach goals and avoidance goals. On a five-point Likert scale, the K-INK measures approach incongruence, avoidance incongruence, and total incongruence. Internal consistency (as measured by Cronbach’s alpha) for the K-INK is reported as ranging between .52 and .87 [81].

#### World Health Organization Quality of Life Assessment (WHO-QoL-BREF)

The WHO-QoL-BREF consists of 26 items and is a standard questionnaire to measure the quality of life [82]. Cronbach’s alpha values range from .66 to .84, indicating an acceptable internal consistency [82]. The WHO-QoL-BREF demonstrates good discriminant validity [82]. In this study, it is administered both in baseline and post assessments and the participants have to indicate their level of agreement on a five-point rating scale with changing answer formats.

#### Rosenberg Self-Esteem Scale (RSES)

The RSES measures self-esteem on a four-point Likert scale. The RSES shows a high reliability and validity for global self-worth [83]. It demonstrates an excellent internal consistency (*Guttman* scale coefficient of reproducibility of .92) [84]. Moreover, the two week test-retest reliability revealed high correlations of .85 and .88, indicating excellent stability [84]. Higher scores on the RSES indicate higher self-esteem.

#### Insomnia Severity Index (ISI)

The ISI is a brief measure for insomnia and is composed of seven items. Each of these items is rated on a five-point Likert scale, ranging from 0 (‘not at all’) to 4 (‘extremely’). Studies reported adequate psychometric properties for ISI versions in English and French [85, 86].

#### Penn State Worry Questionnaire - Abbreviated (PSWQ-A)

The PSWQ [87] is a questionnaire designed to assess the tendency to worry. In this study, an abbreviated eight-item version (PSWQ-A) was used [88]. The measure is scored on a five-point Likert scale from 1 (‘not at all typical’) to 5 (‘very typical’). The PSWQ-A items have good internal consistency highlighted by reported Cronbach’s alpha ranging from .87 to .89 and .94 [88, 89]. Scores for the PSWQ-A range from 8 to 40 [90].

#### Patient Health Questionnaire (PHQ-9)

The PHQ-9 measures depression severity [91]. It scores all nine DSM-IV criteria for depression on a rating scale from 0 (‘not at all’) to 3 (‘nearly every day’). A score of 20 represents severe depression. Internal consistency of the PHQ-9 is excellent with a Cronbach’s alpha of between 0.86 and 0.89 [91]. In this study, the short German version (PHQ-D) was used [92] and the item on suicidality also serves as an indication of the necessity of exclusion from the study.

#### Box Task

In the Box Task [93], participants are confronted with grey boxes on the computer screen, concealing two distinct colours. Participants have to gather information about which of the two colours is more frequent by clicking on said boxes. When they decide that they have gathered sufficient information, they can choose the more frequent colour. This experimental paradigm has been administered in a previous study [94]. If the amount of information an individual gathers before making a decision is low this indicates a tendency to jump to conclusions [27]. Jumping to conclusions has been found to be associated with schizophrenia and delusions [95].

#### Mindful Attention Awareness Scale (MAAS)

The MAAS is a questionnaire measuring mindfulness on a six-point Likert scale. Cronbach’s alpha of the MAAS has been reported as .81 [96].

#### Interpersonal Competence Questionnaire (ICQ)

The ICQ is originally a 40-item questionnaire for the assessment of five domains of interpersonal competence [97]. In this study, only two of the five domains are surveyed: initiation of relationships and negative assertion. Moreover, a recently published short version of the ICQ (called ICQ-15) [98] was used to pick out the six items of the two subscales (three for each domain). The internal consistency of the total scale was high (Cronbach’s alpha = .87) and the reliability coefficients of the subscales were the highest two coefficients of the five subscales: .73 (for initiation of relationships) and .75 (for negative assertion) [98]. The German version of this questionnaire has been validated as well [99].

#### Internalized Stigma of Mental Illness (ISMI) – Short version

The ISMI is a questionnaire measuring the internalized stigma of participants [100]. In this study, the short version of the ISMI was used, which includes 10 items with four-point Likert scales [101]. To evaluate the results, one calculates the mean of those items. A mean score between 1.00 and 2.50 points stands for no internalized stigma, while a mean score between 2.51 and 4.00 stands for high internalized stigma. The German version of the ISMI showed a high internal consistency (Cronbach’s alpha = .92), which was calculated in a study with 139 participants [102].

### Predictors and moderators

#### Medication Adherence Rating Scale (MARS-D)

The MARS [103] consists of five items rated on a five-point Likert scale. These items measure a participant's non-adherent behavior from 1 (‘always’) to 5 (‘never’). A higher score indicates higher adherence to the prescribed medication. MARS-D is the German adaption of this questionnaire developed by Mahler et al. [104]. Internal consistency of the MARS-D (Cronbach’s alpha ranging from .60 to .69) was reported as satisfactory and comparable to the original [104].

#### Attitudes towards Psychological Online Interventions (APOI)

The APOI measures patients’ attitudes towards an online intervention [105]. It reveals certain prejudgments of a study participant, which might influence the outcome parameters and the motivation. Sixteen items are displayed and the level of agreement with each item can be indicated on a five-point rating scale (ranging from ‘no agreement’ to ‘total agreement’). A factor analysis of the APOI showed four dimensions: (a) scepticism and perception of risks (b) confidence in effectiveness (c) technologization threat and (d) anonymity benefits. The APOI shows acceptable to good internal consistency and a good content validity is assumed, because the construction of items was done deductively as well as inductively [105].

#### Credibility/Expectancy Questionnaire (CEQ)

The CEQ is an economic scale to measure treatment expectancy and rationale credibility [106]. The dimensions measured by the CEQ can possibly moderate the outcome. In this study, participants rate items according to two dimensions - one dimension is related to thinking and one is related to feeling. On four of six items, the rating scale ranges from ‘no agreement’ to the treatment rationale to ‘total agreement’ on a nine-point rating scale. For the remaining two items, participants can indicate the subjective symptom improvement from 0% to 100% in steps of 10%. The CEQ demonstrated a high internal consistency of between .84 and .85 [106].

#### University of Rhode Island Change Assessment (URICA)

The URICA [107] is a measure of readiness to change. The 32-item URICA consists of four subscales (eight items each) that correspond to four stages of change (precontemplation, contemplation, action and maintenance) [108]. Internal consistency for the total URICA was reported as excellent (Cronbach’s alpha = .83) [109]. This study used a short version of the German URICA (URICA-S) [110], where items are rated on a five-point Likert scale ranging from 1 (‘not applicable at all’) to 5 (‘very applicable’).

#### Client Satisfaction Questionnaire (CSQ)

The CSQ asks participants to what extent they were satisfied with the intervention [111]. The internal consistency of the CSQ was .93, which stands for an excellent score. There is evidence for a strong construct validity of the CSQ as well [111]. Because it measures treatment satisfaction, it can only be administered at post assessment. Due to its shortness and comprehensiveness, the CSQ is very suitable for mailed surveys [112] and can therefore also be administrated in an online format. The German version (called ZUF-8) [113] is being used in this current study. The eight items can be answered on a four-point rating scale [113].

#### Questionnaire about Side Effects Psychosis and Internet (QueSPI)

This questionnaire assesses the negative effects of internet-based interventions for psychotic patients. It was developed within the research group as part of a pilot study leading up to the current project [114]. Detailed information can be found in the Additional file 1.

### Process measures

#### Working Alliance Inventory – Short Revised (WAI-SR)

As a measure of the weekly variation of the therapeutic alliance, the WAI-SR [114] was included in the study in its German version [115]. It goes back to the Working Alliance Inventory (WAI) [116] and differentiates between goal, task and bond alliance dimensions. Each of those dimensions is represented by four items. The WAI-SR uses a five-point rating scale representing the frequency of positive alliance experiences (ranging from ‘rarely’ to ‘always’). Cronbach’s alpha of the subscale scores ranges from .85 to .90, and of the total scores from .91 to .92, indicating excellent internal consistency [114].

#### Intermediate Assessments Questionnaire

The study group designed a questionnaire to briefly measure symptoms and mental states that were expected to change over the course of the online intervention. Each therapeutic topic covered in the online intervention is represented by a single item in the intermediate assessments questionnaire, such as auditory hallucinations, quality of sleep, self-worth, worry, or depression. Additionally, potentially psychosis-related thinking styles (e.g. jumping to conclusions) are assessed via single items. Five out of 14 items were newly created by the authors, the remaining 9 items were adopted from German versions of established questionnaires (e.g. PHQ-9) [117], or taken and translated from experience sampling studies on schizophrenia (e.g. ‘I feel suspicious‘) [118]. The intermediate assessments questionnaire uses a five-point rating scale ranging from ‘not at all true’ to ‘absolutely true’ and can be read in the Additional file 2.

### Data collection and management

At baseline, participants complete an online assessment including several questionnaires described above. An electronic informed consent and demographic questions will be displayed at the beginning of this online survey. Participants must also indicate their e-mail address and telephone number, which are processed independently from other data. The process of baseline assessment lasts approximately 35 to 40 min. After completion and if no inclusion criteria is not met, a telephone interview with the participant will be arranged. This telephone interview includes two diagnostic interviews (MINI and PANSS, also described above) and the development of an individual emergency plan in case of acute suicidality or psychotic relapse with each participant. The interview lasts approximately 45 to 60 min. If the participant scores below the cutoff on all of the PANSS items (delusions, hallucinations or suspiciousness/persecution), or if the participant reports neither current nor past psychotic symptoms, he or she is excluded from participation and receives a short self-help manual as a compensation for the assessment participation. When inclusion criteria are met, the participants are randomized to one of two groups. The participant either gets access to the online intervention program immediately or after a waiting period of eight weeks. After completion of the intervention period, post assessment and a second telephone interview are administered. The same procedure takes place during the follow-up assessment six months after the intervention period.

### Statistical analyses

Based on the intention to treat sample, a linear mixed-model repeated measures ANOVA with time (T1-T2) as a within-group factor and study condition as a between-group factor will be used for the main research question. Mixed-model repeated measures ANOVA uses all available data of each subject and does not require the substitution of missing values. Sensitivity analysis will be conducted to analyze the impact of dropout on the results. The significance level is set at 5%. We are also interested in possible mediators and/or moderators of the relation between the internet-based self-help intervention and positive psychotic symptoms. We will therefore test whether predictors identified in the literature, such as treatment motivation, working alliance or usage of the intervention could mediate and/or moderate the main effect [119]. To evaluate these possible predictors of treatment outcome, we use change scores of outcome measures as the dependent variables.

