**Methods:**

The intervention includes modules on delusion, voice hearing, social competence, mindfulness, and seven other domains. Participants are guided through the program by a personal moderator. Usage can be amended by an optional smartphone app. In this randomized controlled trial, participants are allocated to a waiting list or an intervention of eight weeks. Change in positive psychotic symptoms of both groups will be compared (primary outcome) and predictors of treatment effects will be assessed.

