### Sample size

A power analysis with the software G*Power [69] resulted in a target sample size of 128 to detect a medium-sized effect (*f* = 0.25) with α = 0.05 and a power of 0.80 for an ANCOVA. Including an assumed attrition rate of about 10%, the final number of participants should reach 140.

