### Randomization

Participants eligible for inclusion will be randomly allocated to one of the two groups (intervention or waiting list control group). Randomization and allocation will be prepared in advance by an independent researcher. This researcher will remain blinded to all processes within the intervention. An automated, web-based randomization service (www.random.org) [72] will be used to generate the randomization list. The allocation ratio will be 1:1.

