### Measures

The primary outcome is the reduction of psychotic symptoms (positive symptoms such as voice hearing and paranoid delusions) at post assessment (directly after the completion of the intervention). Secondary outcomes include the level of symptomatology at follow-up, the number of dropouts and the results of all secondary questionnaires which evaluate quality of life, depression severity, treatment satisfaction, the influence of treatment expectancy, and process measures, among others (see Table 2). Assessments will be completed at baseline, eight weeks and 32 weeks. For an overview of all primary and secondary outcome measures, predictors and moderators, as well as process measures, see Table 2.

**Table 2 Tab2:** An internet-based intervention for people with psychosis (EviBaS): Schedule of enrolment, intervention and assessments

	Study period				
	Enrolment	Allocation	Post-allocation		Close-out
Timepoint	t-1	t0	t1 intervention/waiting period	t2 post assessment	t3 follow-up assessment
Eligibility screen	X				
Informed consent	X				
Allocation		X			
Interventions:					
EviBaS intervention group			X		
Waiting list control group			X		
Assessments:					
Primary outcome measures					
Positive and Negative Syndrome Scale (PANSS)	X			X	X
Mini International Neuropsychiatric Interview (MINI)	X			X	X
Paranoia Checklist	X			X	X
Launay–Slade Hallucination Scale (LSHS-R)	X			X	X
Secondary outcome measures					
Delusion and Voices Self-Assessment (DV-SA)	X			X	X
Rosenberg Self-Esteem Scale (RSES)	X			X	X
Insomnia Severity Index (ISI)	X			X	X
Penn State Worry Questionnaire - Abbreviated (PSWQ-A)	X			X	X
Patient Health Questionnaire (PHQ-9)	X			X	X
Box Task	X			X	X
Mindful Attention Awareness Scale (MAAS)	X			X	X
Interpersonal Competence Questionnaire (ICQ; subscales initiation and negative assertion)	X			X	X
Incongruence questionnaire (K-INK)	X			X	X
World Health Organization Quality of Life Assessment (WHO-QoL-BREF)	X			X	X
Internalized Stigma of Mental Illness – short version (ISMI)	X			X	X
Predictors and moderators					
Medication Adherence Rating Scale (MARS-D)	X			X	X
Attitudes towards Psychological Online Interventions (APOI)	X				
Credibility/Expectancy Questionnaire (CEQ)	X				
University of Rhode Island Change Assessment (URICA)	X				
Client Satisfaction Questionnaire (CSQ)				X	
Questionnaire Side Effects Psychosis and Internet (QueSPI)				X	
Process measures					
Working Alliance Inventory – Short Revised (WAI-SR)		X			

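### The trial is sized for an ANCOVA but will be analysed with a two-wave repeated measures ANOVA, so the stated 0.80 power is not shown for the planned test and a baseline-adjusted analysis would be more precise

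*Protocol article*

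**What the plan says.** The Sample size section reports a G*Power calculation that "resulted in a target sample size of 128 to detect a medium-sized effect". The effect size behind that figure is f = 0.25, and the calculation was run "with α = 0.05 and a power of 0.80 for an ANCOVA". It then adds: "Including an assumed attrition rate of about 10%, the final number of participants should reach 140".

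The Statistical analyses section answers the main research question in the intention-to-treat sample with a different model: "a linear mixed-model repeated measures ANOVA with time (T1-T2) as a within-group factor and study condition as a between-group factor will be used". The reason given is that this model uses all available data and needs no substitution of missing values. The section mentions neither a baseline covariate nor a constraint that the arms share a baseline mean.

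The Abstract (Methods) describes the primary comparison as one of change: "Change in positive psychotic symptoms of both groups will be compared (primary outcome".

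In Table 2 (Measures), the column for t1 is headed "t1 intervention/waiting period" and has no PANSS. The PANSS is marked at enrolment (t-1), post assessment (t2) and follow-up (t3).

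**The concern.** Two sections of the article name two different analyses for the same primary question, and the power statement belongs to the one that will not be run. With a single pre and a single post measurement, the time-by-condition term of a repeated measures ANOVA compares mean change between arms. That is a valid test under randomisation, but it uses the baseline less efficiently than regression adjustment does. The trial is sized at almost exactly 0.80, so there is no margin to absorb a loss of precision. At stake is how far the stated power can be relied on for the one confirmatory test, and precision that could be had from a baseline PANSS already collected.

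**Working it through.** **Inputs.** From the article: N = 128 evaluable, f = 0.25, alpha 0.05 and power 0.80 for an ANCOVA (Sample size), and 1:1 allocation (Randomization). The article gives no pre-post correlation r, so I use 0.3, 0.5 and 0.7 as an assumed range. I also assume equal SDs (σ) at both waves and complete data.

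**Step 1: the plan's own figure.** For a two-group ANCOVA with one covariate, the noncentrality is λ = f²N = 0.0625 × 128 = 8.0, with 1 and 125 degrees of freedom. Power is 0.801, and 128 is the smallest N that reaches 0.80. The figure reproduces. It stays at 128 with zero to three covariates, so no pre-post correlation entered the calculation.

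**Step 2: what the planned model tests.** The article names two factors but not the tested term. With time and condition as factors, and change as the stated comparison, the relevant term is time by condition. With two waves and complete data it equals the difference in mean change.

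- Variance of change per participant: 2(1−r)σ².
- Residual variance in ANCOVA: (1−r²)σ².
- Ratio: 2(1−r)/(1−r²) = 2/(1+r), which is 1.54, 1.33 and 1.18 at r = 0.3, 0.5 and 0.7.

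The ratio exceeds 1 for every r below 1, whichever SD f refers to.

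**Step 3: power at 128 completers.** This depends on which SD f = 0.25 is standardised to, and the article does not say. The change-score test has 1 and 126 degrees of freedom.

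| f refers to | λ, planned test | λ at r = 0.3 / 0.5 / 0.7 | Power, planned test | Power, ANCOVA |
|---|---|---|---|---|
| Covariate-adjusted SD | 8(1+r)/2 | 5.20 / 6.00 / 6.80 | 0.619 / 0.681 / 0.735 | 0.80 at each r |
| Raw SD (d = 0.5) | 8/[2(1−r)] | 5.71 / 8.00 / 13.33 | 0.66 / 0.80 / 0.95 | 0.84 / 0.90 / 0.98, with λ = 8/(1−r²) |
| SD of change | 8 | 8 / 8 / 8 | 0.80 at each r | 0.94 / 0.90 / 0.86, with λ = 16/(1+r) |

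On the first reading, 0.80 needs 196, 170 or 150 completers, each more than the 140 to be recruited. On the second it needs 178, 128 or 78.

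**Step 4: time labels.** The model is said to run from T1 to T2. Table 2 has no PANSS at t1, and the baseline PANSS stands at t-1. The label and the table do not match.

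**The case against.** The strongest reply is that a shortfall in power is not established, and this stands. A reader might infer from the mismatch that the trial will miss 0.80. The article does not support that. If the medium effect means d = 0.5 on the raw SD, the planned test reaches 0.80 at r = 0.5 and exceeds it above. If f is standardised on change, which is how the outcome is described, power is 0.80 at every r. Only the covariate-adjusted reading, which is how the ANCOVA formula treats f, puts power below 0.80 for all r below 1.

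A reader might also argue that the entry rule (a PANSS delusions, hallucinations or suspiciousness item of 3 or more) restricts the baseline range, lowers r and makes matters worse. The direction is wrong. The ratio 2/(1+r) needs equal variances at both waves, and selection on baseline breaks that. In a linear-normal model with r = 0.70 before selection and a cut at the mean, the slope stays at 0.7 and the residual variance at 0.51, while the baseline variance shrinks to 1 − 2/π = 0.363. The variance of change is then 0.51 + 0.3² × 0.363 = 0.543. The ratio to ANCOVA falls from 1.18 to 0.543/0.51 = 1.06, and power on the covariate-adjusted reading rises from 0.735 to 0.777. A cut at the mean of the outcome is in any case not the trial's entry rule, so this shows direction only.

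Nor does the plan throw the baseline away. It enters as a wave of the model and is used inefficiently rather than discarded.

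It can also be said that an unseen analysis plan might add a common baseline mean, and that the tested term is my inference. Both are fair. But the article does name its primary model and its sizing method, and these differ as written. The missing-data rationale does not decide the matter, because a mixed model with a common baseline mean also uses all available data.

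Finally, the T1-T2 label does not mean that the wrong wave would be analysed. No PANSS exists at t1, so this is a labelling slip.

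**Conclusion.** The concern holds in a limited form. The 128 is correct for the ANCOVA named in the Sample size section, but the primary analysis is a different and less precise one. Its variance is 1.18 to 1.54 times that of ANCOVA for r between 0.7 and 0.3, given equal variances at both waves and complete data. The 0.80 is not shown for that analysis. Depending on r and on the SD behind f, neither of which is stated, power at 128 completers lies between 0.62 and 0.95. That the planned test is underpowered cannot be concluded from the article. ANCOVA has the higher power under all three readings over this range of r. The planned test is valid under randomisation, so this is a point that should be fixed for efficiency and consistency, not a flaw that invalidates the trial. The time label is editorial.

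**What to change.** In the Statistical analyses section, make the primary analysis one of these:

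- the week-8 PANSS positive factor compared between conditions, adjusted for the PANSS positive factor at t-1; or
- a likelihood-based mixed model of both waves with a common baseline mean in the two arms. This recovers about the ANCOVA precision, keeps every participant with any available data, and so preserves the stated missing-data rationale.

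The Sample size section then describes the analysis that is run, and should say which SD f = 0.25 refers to. If the present model is kept, restate its power with an assumed r and a defined f. In either case, replace the T1-T2 label with t-1 to t2 so that it agrees with Table 2.

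The cost is a change of wording. No new data, visits or participants are needed.

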### Eligibility criteria

To be included, participants must fulfill all inclusion criteria and not show any exclusion criteria described below. Suffering from other psychiatric disorders such as depression or anxiety disorders (part of the former ‘axis I’ disorders) does not lead to exclusion as long as the schizophrenia spectrum disorder is the primary diagnosis.

Inclusion criteria are:An age of 18 years or older.Provision of electronic informed consent.Access to the internet.Command of the German language.Fulfilling the diagnostic criteria for either schizophrenia, delusional disorder or schizoaffective disorder in their lifetime according to the structured Mini International Neuropsychiatric Interview (MINI) [70] administered during a telephone interview. These diagnoses are allowed to be partly remitted.A score of three or higher on the items assessing delusions (P1), hallucinations (P3) or suspiciousness/persecution (P6) on the Positive and Negative Syndrome Scale (PANSS) [71] showing that some positive symptoms remain.Simultaneous treatment with antipsychotic medication (or regular psychological or psychiatric care in Germany).

Exclusion criteria are:Acute suicidality.Representing an acute danger for others.No agreement on compiling an emergency plan.Diagnosis of an acute neurological disease of the central nervous system that needs to be treated.

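### Moderator and predictor analyses use change scores with no stated baseline adjustment: moderator tests lose precision, and within-arm predictor results depend on how baseline is handled

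*Protocol article*

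**What the plan says.** The Statistical analyses section of the protocol article keeps two things apart. The main question is answered by "a linear mixed-model repeated measures ANOVA with time (T1-T2) as a within-group factor and study condition as a between-group factor". The authors then ask whether variables "such as treatment motivation, working alliance or usage of the intervention could mediate and/or moderate the main effect". For that second purpose the section fixes the outcome form: "To evaluate these possible predictors of treatment outcome", it says, "we use change scores of outcome measures as the dependent variables". No baseline term is mentioned for these models.

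Four other parts of the article bear on the point:
- **Eligibility criteria:** entry requires a score of at least three on one of PANSS items P1, P3 or P6.
- **Primary outcome measures:** those three symptoms belong to the nine-item positive factor that is the primary outcome.
- **Table 2:** motivation (URICA) and expectancy (CEQ) are collected before allocation, hence in both arms.
- **Study design and Intervention:** program access and the moderator's support come with the intervention, which the waiting list receives only after eight weeks.

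**The concern.** A change score contains the baseline value with a negative sign, so it is correlated with baseline severity even when nothing else is going on. The same pre-allocation PANSS interview decides eligibility and supplies the baseline value, so some regression to the mean is to be expected in both arms.

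Two things could follow:
- A variable that merely marks baseline severity could be reported as a predictor of outcome.
- Variation that the baseline score could explain stays in the error term, which weakens interaction tests in a trial sized only for a medium main effect.

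Whether each follows depends on the type of test, so moderators and within-arm predictors need separate treatment.

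**Working it through.** **The plan's own figure.** The article gives no figure for the predictor analyses. Its total of 128, "with α = 0.05 and a power of 0.80 for an ANCOVA", reproduces: a noncentral F test with f = 0.25 and 1 numerator degree of freedom has power 0.801 at N = 128 and 0.798 at N = 127. I therefore use 64 per arm and two-sided 5%.

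**Assumptions.** The article gives neither the pre-post correlation r nor the predictor-baseline correlation. I take r = 0.5 and 0.7, a predictor-baseline correlation of 0.3, and equal pre and post SDs (set to 1).

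**Step 1. Moderators: bias.** Under randomisation the relation between baseline and change is the same in both arms, so it drops out of the predictor-by-condition term. In simulation (5,000 runs, 64 per arm, predictor-baseline correlation 0.3 or 0.5), the unadjusted change-score interaction test rejects a true null 4.7% to 5.3% of the time.

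**Step 2. Moderators: precision.**
- Residual variance of change: 2(1 − r).
- Residual variance adjusted for baseline: 1 − r² = (1 − r)(1 + r).
- Ratio: 2/(1 + r) = 2/1.5 = 1.33 at r = 0.5, and 2/1.7 = 1.18 at r = 0.7.
- Cut in standard error from adjusting: 1 − √((1 + r)/2) = 13% at r = 0.5, and 8% at r = 0.7.
- In power terms, suppose a moderator test on change scores has power 0.60. Its standardised effect is 1.96 + 0.253 = 2.213. Dividing by √0.75 = 0.866 gives 2.556, and power becomes Φ(2.556 − 1.96) = 0.72 at r = 0.5.

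The direction does not depend on equal SDs. If the baseline SD is k times the post SD, the two residual variances differ by (1 + k² − 2rk) − (1 − r²) = (k − r)², which is never negative. The size does depend on it: with k = 0.8 and r = 0.5 the ratio is 0.84/0.75 = 1.12.

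**Step 3. Within-arm predictors, first null.** The predictor is unrelated to the post score given the observed baseline.
- Correlation of baseline with change: −√((1 − r)/2) = −0.50 at r = 0.5, and −0.39 at r = 0.7.
- Induced correlation of the predictor with change: 0.3 times that, −0.15 and −0.12.
- Simulated false-positive rate at n = 64, unadjusted: 21% and 15%. With baseline as covariate it is about 5%.
- If main effects were tested with both arms pooled (n = 128), the unadjusted rates would be 39% and 25%.
- If the predictor-baseline correlation is zero, all rates are about 5%.

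**Step 4. Within-arm predictors, second null.** True severity is stable, pre and post scores are truth plus error, and the predictor is related to true severity but not to its change.
- Covariance of predictor with change: 0.3 − 0.3 = 0, so the change-score test holds about 5%.
- Partial correlation of predictor with post score given baseline: 0.3(1 − r)/√((1 − 0.3²)(1 − r²)) = 0.15/√(0.91 × 0.75) = 0.18 at r = 0.5, and 0.09/√(0.91 × 0.51) = 0.13 at r = 0.7.
- Fisher z rejection rate at n = 64: atanh(0.182) × √60 = 1.42, or 30%; atanh(0.132) × √60 = 1.03, or 18%.
- Pooled at n = 128 (√124): 53% and 32%.

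So the error moves from one analysis to the other according to which null is true. The adjusted interaction test keeps about 5% under both nulls.

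**The case against.** A reader might infer that any predictor correlated with baseline severity will appear to predict improvement, and that adjusting for baseline is a free cure. The documents do not support this, for four reasons.

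- **Moderation is named explicitly**, and that test keeps its type I error.
- **The spurious correlation is modest and often undetected.** It arises only for main-effect or within-arm tests, and its direction follows the sign of the predictor-baseline correlation.
- **It depends on which null holds.** Regression to the mean comes from error or passing fluctuation in the observed baseline. A predictor tied to stable severity need not inherit it, and adjustment then creates the false positive (Step 4). The predictors are online self-reports and the PANSS is a telephone interview, so shared rating error is not obvious. The article does not say which model applies.
- **A change score is not in itself a fault.** With the baseline score as covariate it gives the same predictor coefficient and test as the adjusted post score. The article does not say the change scores will be analysed unadjusted, and a covariate list may sit in an analysis plan not shown.

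All four stand and limit the point. They do not remove it. The article commits to an outcome form and, as written, leaves the baseline term out. For moderators, including it costs one degree of freedom. For working alliance and usage there is no waiting-list value before week 8, so the protection given by randomisation is not available.

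**Conclusion.** The point holds in a limited form.

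- **Moderators measured in both arms:** no bias, but avoidable loss of precision. Residual variance is 33% higher at r = 0.5 and 18% higher at r = 0.7, assuming equal pre and post SDs. The loss is smaller if selection at entry has narrowed the baseline spread.
- **Working alliance, usage and other main-effect predictors:** a change-score analysis alone can mistake baseline severity for prediction (about 21% or 15% false positives at n = 64 under the first null). A baseline-adjusted analysis alone can err as much or more under the second null (about 30% or 18%). All these rates rest on an assumed predictor-baseline correlation of 0.3. Neither analysis is sufficient by itself.

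The primary mixed-model analysis is untouched. This is a worthwhile improvement to secondary analyses and does not threaten the trial's main conclusion.

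**What to change.** Amend the last sentences of Statistical analyses to say three things:

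1. Moderators are tested with the t2 score (or, equivalently, change) as dependent variable. The terms are the t-1 score of the same measure, condition, predictor and predictor-by-condition, with both arms included.
2. For within-arm and main-effect predictors, including working alliance and usage, the baseline-adjusted and the change-score results are reported side by side. A finding that appears in only one of them is described as dependent on the handling of baseline severity.
3. Within-arm results are described as associations among treated participants, not as moderation of the treatment effect.

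The baseline scores are already collected. The cost is a few sentences, one degree of freedom per moderator model, and one extra result per within-arm or main-effect predictor.
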